#### Quality of life

The translated, adapted and validated Brazilian version [33] of the Oral Health Impact Profile, in its simplified form (OHIP-14) [34], will be used to assess the oral health-related quality of the participants. This questionnaire contains 14 questions, divided into seven subscales: functional limitation, physical pain, physiological discomfort, physical disability, physiological disability, social disability and handicap. The questions will be answered on a 5-point Likert scale, the responses will be summarized and the final score will be calculated.

The translated version of the Patient-Reported Oral Mucositis Symptoms (PROMS) scale will also be used to assess the OM effects reported by the patient [35]. This scale was originally used to assess OM due to CT; however, its use in patients undergoing RT is also feasible [36, 37]. The scale contains 10 questions, which are answered on a 10-cm uninterrupted visual analog scale. The participant will be asked to indicate the score for each item. The sum of the 10 items will be used as the PROMS score.

These instruments will be applied during the first appointment and after the 7th, 14th, 21st and 30th RT sessions based on previous studies [23, 38] that also evaluated the QoL weekly. As reported earlier, the OM evaluation will occur at the same time points. The questionnaires will be applied before the PBMT session and if the participant is not able to answer, a calibrated healthcare professional will provide help.

#### Saliva collection and analysis

The collection of saliva will be performed before initiating the HNC treatment and after the 7th, 14th, 21st and 30th RT sessions, based on the method of Oton-Leite et al. [28] and Navazesh [39]. The participants will be instructed not to eat or drink 1 h before the collection of saliva.

The collection of unstimulated saliva will be performed in an artificial light environment, with the participants sitting with their eyes open, with their head slightly tilted down, without talking, opening their mouth or swallowing the saliva during the time of collection. Initially, the participants will be instructed to wash their mouth with water and swallow any saliva in their mouth. The participants will then be instructed not to swallow for a period of 5 min in order to accumulate saliva. This accumulated saliva will be deposited in a sterile Falcon-type millimeter tube.

The sample will be centrifuged for 15 min at 4500 rpm. The samples will then be transferred to another tube and diluted (1:1) in PBS solution (0.4 mM NaCl and 10 mM NaPO_4_) containing protease inhibitors (0.1 mM phenylmethylsulfonyl fluoride, 0.1 mM benzethonium chloride, 10 mM EDTA and 0.01 mg/ml aprotinin A) and 0.05% Tween-20. The solution will be homogenized, distributed in aliquots of approximately 2 ml and frozen at − 80 °C. The concentrations of inflammatory cytokines, nitrite and total proteins will be assessed in each saliva sample.

#### Inflammatory study

##### Cytokine study

The concentrations of the cytokines (IL-1β, IL-10, IL-6, IL-8, IL-12, TNF-α) in the saliva samples will be determined by cytometric bead array (CBA). The CBA method enables the detection of multiple soluble mediators from a relatively small sample, using bead-based flow cytometric immunoassays, since beads of different sizes or colors are used. Thus, this assay measures the levels of the six cytokines in a small sample of saliva [40].

The cytokines will be measured by a BD FACSCanto II flow cytometer (BD Biosciences, San Jose, CA, USA) using the CBA human inflammatory cytokines kit (BD Biosciences) following the manufacturer’s recommendations. Briefly, the Human Chemokine Standards will be reconstituted and serially diluted in the Assay Diluent. After this, the Human Chemokine Capture Beads will be mixed and a 10-μl aliquot of each Capture Bead, for each assay tube to be analyzed, will be placed into a single tube. A 96-well plate will be used to perform the assay. The initial wells will be filled with 50 μl of the Human Chemokine Standard; then, 50 μl of the saliva sample will be placed, followed by the addition of 50 μl of the Human Chemokine PE detection reagent. The saliva and detection reagents will be incubated for 3 h, protected from light. After this, 100 μl of wash buffer will be added to each well and centrifuged at 1100 rpm for 5 min. The supernatant will be carefully aspirated and discarded. Finally, the bead pellet will be resuspended with the addition of 150 μl of wash buffer. The values will be determined based on the negative control and a standard curve.

The Bradford method will be used to measure the total protein concentration in the saliva samples, expressed as milligrams per milliliter. This concentration will be used to adjust the salivary cytokine values for each sample. The values of the cytokine levels in saliva samples corrected for total proteins will be expressed as picograms per milligrams of protein.

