##### Nitrite concentration

The concentration of nitrite in the saliva samples will be measured using the method described by Green et al. [41]. A volume of the saliva sample will be transferred to a 96-well plate and then the same volume of the Griess reagent will be added to each well. After 10 min, the absorbance will be measured by a spectrophotometry reader (SpectraMax 340; Molecular Devices) using a 570-nm filter. A standard curve will be used to calculate the nitrite concentrations.

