### Statistical analysis of data

The comparison of the clinical and demographic characteristics of the participants between the two groups will be performed using the Pearson chi-square test for categorical variables. The Mann–Whitney test will be used to compare the severity of OM and concentration of cytokines between the two groups. The Friedman test will be used to compare changes in outcomes in the different time points for each of the treatment groups. In case of nonrejection of the null hypothesis, a post-hoc power analysis will be performed to test whether the study has sufficient power to identify the differences between groups. Values of *p* < 0.05 will be considered statistically significant. The statistical analysis will be performed using the IBM SPSS 20.0 statistical package (SPSS Inc., Chicago, IL, USA).

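### Cytokines are expressed per mg of salivary total protein, a denominator that may differ by arm after randomisation, and the plan neither names the tested scale nor compares total protein between arms

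*Protocol article*

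**What the plan says.** The relevant text lies in four places of the protocol article.

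- **Saliva collection and analysis.** Saliva is taken before cancer treatment and after the 7th, 14th, 21st and 30th radiotherapy sessions. Three kinds of analyte are measured every time: "The concentrations of inflammatory cytokines, nitrite and total proteins will be assessed in each saliva sample".
- **Cytokine study.** The denominator is defined by "The Bradford method will be used to measure the total protein concentration in the saliva samples, expressed as milligrams per milliliter". Then: "This concentration will be used to adjust the salivary cytokine values for each sample". The values "corrected for total proteins will be expressed as picograms per milligrams of protein". No other expression of the cytokine result is named in this section.
- **Nitrite concentration.** "A standard curve will be used to calculate the nitrite concentrations". No protein correction is mentioned, and no reason is given for handling nitrite differently.
- **Statistical analysis of data.** "The Mann–Whitney test will be used to compare the severity of OM and concentration of cytokines between the two groups". The text does not say whether this means pg/ml or pg per mg of protein. It names no between-arm test for total protein or for nitrite.

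The Background section makes an effect of PBMT on inflammatory and oxidative stress proteins part of the study hypothesis.

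**The concern.** Dividing by total protein gives a clean cytokine comparison only if total protein does not itself differ between arms because of treatment. Here the denominator is measured after randomisation, at the same visits as the cytokines. Under Oral mucositis evaluation, severe disease includes large confluent ulcers and ulcers with necrosis and bleeding. Under Participants, severe disease is expected in 60% of controls and 21% of the PBMT group. Saliva pooled in such mouths could plausibly carry more protein, and more often in controls.

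If that happened, a difference in pg per mg could come from the numerator, the denominator or both. With no between-arm comparison of total protein, a reader could not tell which. A conclusion that PBMT does, or does not, modulate cytokines could then rest on protein alone.

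**Working it through.** **1. The plan's own figure.** The only related figure is the sample size, which rests on severe mucositis. With rates 0.60 and 0.21, mean rate 0.405, two-sided alpha 0.05 and power 80%:

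n per arm = (1.960 + 0.842)² × 2 × 0.405 × 0.595 / 0.39² = 24.87, so 25 per arm and 50 in total.

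This reproduces the stated 50. It says nothing about cytokines, for which the plan gives no expected difference or power. It supplies the 60% and 21% used below.

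**2. The identity.** Let C be the cytokine concentration and T total protein. On geometric means:

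(control/PBMT ratio of C/T) = (control/PBMT ratio of C) ÷ (control/PBMT ratio of T).

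This is arithmetic and needs no assumption.

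**3. Illustrative size.** Assume severe mucositis multiplies T by p, that nothing else shifts T between arms, and that the severe rates at the visit differ by d. The control/PBMT ratio of T is then p^d, and the corrected cytokine ratio is multiplied by p^(−d).

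| Assumed p | d = 0.60 − 0.21 = 0.39 | d = 0.20 (assumed smaller gap) |
|---|---|---|
| 1.5 | 0.85 | 0.92 |
| 2 | 0.76 | 0.87 |
| 3 | 0.65 | 0.80 |

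At p = 2 and d = 0.39, a true PBMT/control cytokine ratio of 0.76 (a 24% reduction) would show as no difference in pg per mg. The second column is there because the documents give no severe rate by visit.

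**4. Effect on the planned test.** A Mann–Whitney test was simulated with 25 per arm and 4,000 runs per scenario. Cytokine and protein were independent and log-normal, with assumed log-SDs of 0.8 and 0.5. The second column gives the p that would produce each protein ratio r at d = 0.39, from p = r^(−1/0.39).

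| PBMT/control protein ratio | Implied p | Ratio test rejects, cytokine equal | Ratio test rejects, cytokine halved by PBMT |
|---|---|---|---|
| 1.0 | 1.0 | 4.5% | 70.6% |
| 0.8 | 1.8 | 11.9% | 37.6% |
| 0.67 | 2.8 | 29.0% | 16.9% |
| 0.5 | 5.9 | 68.8% | 5.2% |

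In the same scenarios the test on unadjusted cytokine rejects 4.3% to 5.0% with no effect and 81.3% to 83.2% with cytokine halved. The last row lies outside the p range of step 3. The simulation contains no shared saliva-concentration factor, so it shows how a protein shift matters. It does not show that pg/ml is the better scale.

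**The case against.** The strongest reply is that protein correction is a reasonable choice. If a sample is more concentrated by a factor f, both analytes rise together, and (C × f)/(T × f) = C/T, so the ratio removes f. An unadjusted pg/ml value has the opposite weakness: it moves with saliva concentration, which may also differ by arm. This stands. Using the ratio is not in itself an error, and there is no case here for making pg/ml the sole leading scale.

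Three stronger readings are tempting, and the documents support none of them.

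- *Cytokines will be analysed only as a ratio.* The Cytokine study section names only the corrected unit, but unadjusted concentrations are measured in every sample and the statistical section speaks of concentration. The text shows an unnamed scale. It does not exclude the unadjusted value.
- *The ratio is biased against PBMT.* No section says that ulceration, radiotherapy or PBMT changes salivary total protein. Direction and size both rest on an assumed p. The planning rates are also not stated for any single visit, so the figures at d = 0.39 may overstate the effect.
- *Nitrite and cytokines contradict each other.* The nitrite section describes an assay, and nothing claims that the markers share a basis. The different handling is unexplained, which is a smaller matter.

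It can also be said that an article may leave such detail to a fuller plan. That covers which tables are shown. It does not fully cover the analysis variable, because the article itself states the protein correction and then describes the tested quantity in words that fit either scale.

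Finally, cytokines do not drive the sample size, and the Outcomes section places them after severe mucositis and quality of life. That limits the weight of the point.

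**Conclusion.** The point holds in a limited form. The article fixes a cytokine expression whose denominator is measured after randomisation and could plausibly differ by arm. It does not say which scale the Mann–Whitney test uses, and it names no between-arm check of total protein. A protein difference could therefore be read as cytokine modulation, or could hide it.

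The identity in step 2 is certain. The size is not: a factor of 0.85 to 0.65 on the control-to-PBMT ratio holds only if severe mucositis multiplies protein by 1.5 to 3 and the 60% versus 21% gap applies at the visit analysed. It is nearer 1 if the gap is smaller, and exactly 1 if protein is unaffected. The rejection rates rest further on assumed SDs and on independence of cytokine and protein. The point bears on the mechanistic hypothesis. It does not touch the sample size or the severe-mucositis comparison.

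**What to change.** In the Cytokine study and Statistical analysis of data sections:

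1. State which cytokine scale is tested and name it as leading. The protein-corrected value may be kept.
2. Compare the unadjusted concentration (pg/ml) and total protein itself between arms beside it.
3. Use each participant's pre-treatment saliva value as a covariate in these comparisons, for example in a model on the log scale.
4. Present nitrite both unadjusted and protein-corrected.
5. State that cytokine modulation will be claimed only if it is not confined to the ratio.

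**Cost.** Cytokines, nitrite and total protein are already measured in every sample, including the one before treatment, so no new sample or assay is needed. There are a few more results per marker, which is why one scale should be named as leading. The baseline-adjusted comparison goes beyond the planned Mann–Whitney test and would need a sentence of its own in the statistical section.

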##### Nitrite concentration

The concentration of nitrite in the saliva samples will be measured using the method described by Green et al. [41]. A volume of the saliva sample will be transferred to a 96-well plate and then the same volume of the Griess reagent will be added to each well. After 10 min, the absorbance will be measured by a spectrophotometry reader (SpectraMax 340; Molecular Devices) using a 570-nm filter. A standard curve will be used to calculate the nitrite concentrations.

### Economic analysis

#### Study perspective and setting

The cost-effectiveness evaluation will be performed from the health provider perspective and conducted alongside the randomized clinical trial. The setting considered was the Dental Care Service of the hospital, which includes a dental office and a waiting room, and the staff comprise a dentist licensed in PBMT and a dental assistant.

#### Estimation of costs

##### PBMT costs

Cost estimation will include the direct costs of resources associated with the treatment of OM during RT. All fixed and variable costs will be identified, measured and valuated for each cost item. The variable costs will include consumable items (70% ethanol, gauzes, procedure gloves, etc.). The fixed costs will include the income of the professionals and costs associated with the laser equipment. For the equivalent annual cost (EAC) of durable goods, a discount rate of 5% and a usage life of 5 years will be considered for calculation, using the following formula:$$ \mathrm{EAC}=\left(n\times x\right)/\left(1-1/\left[{\left(1+n\right)}^t\right]\right) $$

where EAC = annual cost equivalent, *t* = useful life, *x* = purchase price and *n* = discount index.

The average cost per PBMT session will be calculated as the sum of the variable and fixed costs. The cost of staff will consider the value of the work hours proportional to the time spent in each session: (Monthly wage / monthly working time) × time spent.

The data on costs of consumables will be obtained from the administrative department of the hospital and the cost of the laser equipment will be based on mean market prices. Costs will be estimated in Brazilian currency (Brazilian Real (BRL)) and later converted to international dollars using the purchasing power parity exchange rate.

The costs of RT and CT and those related to the routine preventive oral health protocol will not be considered since they are similar for both groups. Besides that, the social costs related to wider societal costs (e.g., loss of productivity resulting from treatment, family costs, etc.) will not be considered. Similarly, other capital costs or those associated with implementation of the dental care service will not be included.

##### Costs due to severe OM

The costs related to OM will include episodes of severe OM (WHO degrees III and IV), hospitalizations, use of opioid analgesics and parenteral nutrition. These data will be retrieved from the hospital records and cost estimation will be based on the governmental database for the public health system.

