### Study groups

#### Group 1: photobiomodulation therapy

The participants in this group will be submitted to laser therapy five times a week, during the RT. The PBMT protocol will begin in the first RT session, be conducted before each RT session and continue until the end of the treatment. Since the RT sessions will be scheduled in a specific hour, it will be possible to control participant appointments. If severe OM develops at the end of the RT, the patient will receive additional sessions.

The Twin Flex Evolution Laser (MMOptics, São Paulo, Brazil) will be used at a wavelength of 660 nm (red laser), 25 mW of power, in continuous mode, with punctual and perpendicular application in contact with the mucosa. The transferred energy will be 6.2 J/cm^2^ for 10 s on a spot area of 0.04 cm^2^, and thus energy of approximately 0.25 J will be deposited at each point. Before each session, the tip of the laser will be disinfected with a solution of 70% alcohol and wrapped in a plastic film. The laser beam will not be irradiated in a malignant lesion smaller than 1 cm if observed, or near a surgical site.

Specific anatomical regions be considered for the PBMT: right and left buccal mucosa (10 points on each side), upper and lower labial mucosa (four points on each lip), hard palate (three points), lateral surface of the tongue (10 points on each side), soft palate (three points), dorsal tongue (three points), floor of the mouth (two points) and labial commissure (one point on each side). This protocol is based on a previous study by Oton-Leite et al. [30].

The participants will also be submitted to a dental care protocol that consists of elimination of the infection focus, a fluoride rinse, a chlorhexidine 0.12% rinse three times a day diluted in water in a 1:1 proportion, recommendation to drink at least 1.5 L of water per day and the maintenance of good oral hygiene. If the presence of OM is observed, an oral ointment with hydrocortisone 5 mg, neomycin 5 mg, troxerutin 20 mg, ascorbic acid 0.5 mg and benzocaine 2 mg will be prescribed (Gingilone; Farmasa, São Paulo, Brazil).

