#### Group 2: control group

The participants in the control group will have laser therapy appointments; however, they will not be irradiated. A simulation of the irradiation will be conducted by turning on the equipment, which produces the characteristic sound of the laser device, but the laser will not be irradiated. As mentioned for the PBMT group, if participants present with severe OM at the end of treatment, they will be submitted to PBMT. The participants will also be submitted to laser therapy in cases of RT suspension due to severe OM, during the suspension interval, to speed up the healing process.

The participants in the control group will be submitted to the dental care protocol. This protocol consists of elimination of the infection focus, a fluoride rinse, a chlorhexidine 0.12% rinse three times a day diluted in water in a 1:1 proportion, a recommendation to drink at least 1.5 L of water and the maintenance of good oral hygiene. In the presence of OM, Gingilone (Farmasa), an oral ointment with hydrocortisone 5 mg, neomycin 5 mg, troxerutin 20 mg, ascorbic acid 0.5 mg and benzocaine 2 mg, will be used. At the end of the RT treatment, the participants in this group will also receive PBMT if needed.

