#### Oral mucositis evaluation

An assessor who is blinded to the treatment will conduct the OM evaluation. The researcher responsible for the PBMT will take intraoral pictures and save them on a hard disk for later evaluation. The evaluation will be in the first appointment and after the 7th, 14th, 21st and 30th RT sessions. The photographs will be taken using a T3i camera, with a circular flash (MR-14EX II) and a lens of Ef-s 18–55 mm F/3.5–5.6 (Canon, Tokyo, Japan). Pictures of the upper and lower labial mucosa, buccal mucosa, hard and soft palate, lateral surface of the tongue and floor of mouth will be acquired.

For the OM classification, the World Health Organization (WHO) [31] and the National Cancer Institute (NCI) [32] classifications will be used.

According to the WHO scale, the OM is classified as: 0, no signs or symptoms; 1, oral soreness and erythema; 2, erythema, ulcer, both solid and liquid diets tolerated; 3, ulcers and liquid diet only; 4, oral alimentation is impossible. The NCI scale is a graduated scale as follows: 0, no visible alterations; 1, presence of erythema; 2, noncontiguous ulcers up to 1.5 cm in diameter; 3, contiguous ulcers larger than 1.5 cm in diameter; 4, ulcers showing necrosis and bleeding. In this study, OM will be considered severe when classified with grades 3 or 4 according to the NCI and/or WHO scales.

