### Cost-effectiveness analysis

The incremental cost-effectiveness ratio (ICER) will be calculated considering the incidence of severe degrees of OM as the measure of effectiveness for the PBMT and control groups. We will also measure the effectiveness based on patient-reported outcomes (including QoL measures). A decision tree-type diagram will be created to represent all clinically relevant events.

The ICER will be calculated to determine the cost-effectiveness of PBMT. The ICER will be calculated by dividing the cost difference (Cost2 – Cost1) by the difference between the frequency of severe OM in both groups. The ICER will represent the incremental cost to avoid one case of severe OM using PBMT.

Additionally, another ICER will be calculated by dividing the cost difference (Cost2 – Cost1) by the difference between the QoL in both groups. The ICER represents the incremental cost to avoid the loss of 1 point on the QoL measure, assessed using the difference between the last evaluation (30th RT) and the baseline (0 RT). Two different ICERs will be calculated considering the scores of each instrument (OHIP-14 and PROMS). The following formula summarizes the ICER analysis.$$ \mathrm{ICER}=\left(\mathrm{Cost}2-\mathrm{Cost}1\right)/\left(\mathrm{QoL}2-\mathrm{QoL}1\right) $$

Univariate sensitivity analysis will be performed to assess the uncertainty in the parameters associated with PBMT.

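### The severe-OM ICER costs episodes on the WHO scale but counts cases on NCI and/or WHO, and its RT-only cost window leaves out active laser that the protocol gives after RT in both arms

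*Protocol article*

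**What the plan says.** Four parts of the protocol article bear on this point.

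- **Effect.** The section Oral mucositis evaluation fixes the case definition: "In this study, OM will be considered severe when classified with grades 3 or 4 according to the NCI and/or WHO scales". Grading is done from photographs by a blinded assessor. The section Cost-effectiveness analysis divides the cost difference "by the difference between the frequency of severe OM in both groups" and interprets the result as the cost of avoiding one severe case.
- **OM costs.** The section Costs due to severe OM states: "The costs related to OM will include episodes of severe OM (WHO degrees III and IV), hospitalizations, use of opioid analgesics and parenteral nutrition". The source is different from that of the effect: "These data will be retrieved from the hospital records".
- **Cost window.** The section PBMT costs states: "Cost estimation will include the direct costs of resources associated with the treatment of OM during RT". The abstract likewise ties costing to the radiotherapy interval.
- **Extra laser.** For the PBMT arm: "If severe OM develops at the end of the RT, the patient will receive additional sessions". For controls: "At the end of the RT treatment, the participants in this group will also receive PBMT if needed". The control-group section refers back to the PBMT arm for the trigger, severe OM at the end of treatment. It also gives controls active laser while RT is suspended for severe OM. No section says how any of these sessions are costed.

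**The concern.** A cost per severe case avoided is easy to interpret only if the numerator picks up the cost of the events that the denominator counts. Here an episode graded severe on NCI but not on WHO enters the denominator, and its episode cost is outside the stated numerator. Such cases are plausible on the article's own definitions. WHO grades 2 and 3 are separated by diet, whereas NCI grades what can be seen of the ulcers, and the assessor sees only photographs.

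The cost window raises a second problem. The laser session is the technology whose cost the study sets out to measure, yet sessions delivered under the protocol after RT fall outside the window.

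The definition mismatch affects the severe-OM ICER. The incomplete costs reach further, because the same cost difference is the numerator of the OHIP-14 and PROMS ICERs. The planned univariate sensitivity analysis is described as covering PBMT parameters, and nothing says that it varies the severity definition or the horizon. The results are intended for public policy-makers.

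**Working it through.** **What can be reproduced.** The article gives no ICER and no unit cost for this trial. Its only computed design figure is the sample size, which supplies the two rates used here: 60% severe OM in controls and 21% with PBMT.

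- Odds ratio: (0.21/0.79)/(0.60/0.40) = 0.177, matching the stated 0.18.
- Kelsey formula with two-sided alpha 0.05 and 80% power: (1.960 + 0.842)² × 2 × 0.405 × 0.595 / 0.39² = 24.87. This gives 25 per group and 50 in total, as stated.

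The rates are therefore consistent with the design. The sample size itself does not bear on the point.

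**Inputs that the documents do not give (assumed).** Costs are in units of one severe episode, excluding the separately listed hospitalization, opioid and nutrition items.

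- s = share of severe cases (NCI and/or WHO) that are also WHO III-IV, taken as equal in both arms.
- h = share of severe cases still severe at the end of RT, taken as 0.5 in both arms.
- r = cost of post-RT laser per such case.

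**Formulas.** With severe-OM rate p in an arm, the omitted cost per patient is p × [(1 − s) + r × h].

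- Ratio of omissions, control to PBMT: 0.60/0.21 = 2.86, whatever s, r and h are, provided they are equal across arms.
- Excess in the ICER: (0.60 − 0.21) × [(1 − s) + r × h] / 0.39 = (1 − s) + r × h.

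| s | r | Omitted, control | Omitted, PBMT | ICER too high by (episode costs) |
|---|---|---|---|---|
| 1.0 | 0 | 0 | 0 | 0 |
| 1.0 | 0.25 | 0.075 | 0.026 | 0.125 |
| 0.8 | 0 | 0.120 | 0.042 | 0.200 |
| 0.8 | 0.25 | 0.195 | 0.068 | 0.325 |
| 0.6 | 0.25 | 0.315 | 0.110 | 0.525 |

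These rows show how the error behaves; they do not estimate it. They also treat an NCI-only episode as costing as much as a WHO III-IV episode, which may be too much.

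**Can the direction reverse?** Yes, if s differs by arm. Take s = 0.9 in controls and the definition mismatch alone. Controls omit 0.60 × 0.10 = 0.060. The PBMT arm omits more than this once 0.21 × (1 − s) > 0.060, that is, once its s falls below 1 − 0.060/0.21 = 0.71.

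**Suspension laser.** This is written for controls only. If it is not costed, the omission falls entirely on controls. If suspension counts as part of RT, nothing is lost. The text does not settle which.

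**The case against.** The other side has several fair points.

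- **Not only WHO III-IV cases are costed.** A reader might infer that nothing is costed for an NCI-only case. The text does not support that, because hospitalizations, opioids and parenteral nutrition are listed as further items with no WHO condition. This stands and limits the mismatch to the episode cost itself. An NCI-only case is at most WHO grade 2, where solid and liquid diets are tolerated, so its cost may be modest.
- **Controls are not said to receive more laser after RT.** A reader might infer this from 60% versus 21%. The trigger is the same in both arms, and those planning rates are not described as rates at the end of RT. This stands.
- **Dollar amounts.** It is tempting to price the gap with the US cost figures in the Background. Those include hospital days and opioid use, which the plan keeps, and the NCI-only share would have to be invented. This stands, and no dollar figure is offered.
- **An ICER numerator is a difference in arm costs, not a sum over counted cases.** This is true, so the two definitions do not invalidate the ratio in principle. However, the plan itself builds an episode cost into the numerator and gives it a narrower definition than the effect.
- **An RT-bounded horizon is a stated choice that fits the last assessment at session 30.** This stands as a reason not to follow OM costs to resolution, since no later assessment is planned. It does not explain leaving out laser sessions that the protocol itself delivers.
- **Charging rescue PBMT to controls moves that arm away from usual care in the public system.** This is arguable. Reporting the RT-only horizon alongside shows how much depends on the post-RT sessions.

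**Conclusion.** The point holds as an internal inconsistency in the economic analysis. Severe OM is defined one way for the effect and more narrowly for the episode costs. The cost window excludes active laser given in both arms after RT, and the costing of control-arm laser during suspension is left unclear. Costs are therefore incomplete in both arms.

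If omitted costs track severe OM at the planned 60% and 21%, with equal shares and unit costs across arms, the omission per patient is 0.60/0.21 = 2.86 times larger in controls, and the ICER per case avoided is too high against PBMT. A reader might take bias against PBMT as established. It is not: it rests on those equal shares, it disappears if all severe cases are also WHO III-IV and post-RT laser costs nothing, and it can reverse if NCI-only cases are sufficiently more common among severe cases in the PBMT arm. The documents do not allow the size to be computed.

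**What to change.** 1. Use the definition in Oral mucositis evaluation for both the episode costs and the effect. Where hospital records do not carry an NCI grade, the trial's own blinded grading can identify the episode.
2. Charge every active PBMT session delivered under the protocol, including sessions during RT suspension and after RT, to the arm that received it, by the same rule in both arms.
3. Report the RT-only horizon as a stated sensitivity analysis for all three ICERs.

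This changes analysis wording only and leaves every treatment rule as it is. The cost is a slightly longer extract of session and hospital records, and a cost window slightly longer than the effect window, which ends at session 30. Following all OM costs to resolution is not asked for, because no assessment is planned after that session.
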